# A randomized phase II study of nutritional and exercise treatment for elderly patients with advanced non-small cell lung or pancreatic cancer: the NEXTAC-TWO study protocol

**DOI:** 10.1186/s12885-019-5762-6

**Published:** 2019-05-31

**Keywords:** Cachexia, Elderly patients, Lung cancer, Pancreatic cancer, Multimodal intervention

## Abstract

**Background:**

Most advanced elderly cancer patients experience fatigue, anorexia, and declining physical function due to cancer cachexia, for which effective interventions have not been established. We performed a phase I study of a new nonpharmacological multimodal intervention called the nutritional and exercise treatment for advanced cancer (NEXTAC) program and reported the excellent feasibility of and compliance with this program in elderly patients with advanced cancer who were at risk for cancer cachexia. We report here the background, hypothesis, and design of the next-step multicenter, randomized phase II study to evaluate the efficacy of the program, the NEXTAC-TWO study.

**Methods:**

Patients with chemo-naïve advanced non-small cell lung cancer or pancreatic cancer, age ≥ 70 years, performance status ≤2, with adequate organ function and without disability according to the modified Katz index will be eligible. In total, 130 participants will be recruited from 15 Japanese institutions and will be randomized into either the intervention group or a control group. Computer-generated random numbers are allocated to each participant. Stratification factors include performance status (0 to 1 vs. 2), site of primary cancer (lung vs. pancreas), stage (III vs. IV), and type of chemotherapy (cytotoxic vs. others). Interventions and assessment will be performed 4 times every 4 ± 2 weeks from the date of randomization. Interventions will consist of nutritional counseling, nutritional supplements (rich in branched-chain amino acids), and a home-based exercise program. The exercise program will include low-intensity daily muscle training and lifestyle education to promote physical activity. The primary endpoint is disability-free survival. It is defined as the period from the date of randomization to the date of developing disability or death due to any cause. This trial also plans to evaluate the improvements in nutritional status, physical condition, quality of life, activities of daily living, overall survival, and safety as secondary endpoints. Enrollment began in August 2017. The study results will demonstrate the efficacy of multimodal interventions for elderly cancer patients and their application for the maintenance of physical and nutritional conditions in patients with cancer cachexia. This work is supported by a grant-in-aid from the Japan Agency for Medical Research and Development.

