## Background

Advances in cancer therapy have been extended not only to combinations of cytotoxic chemotherapy but also to immunotherapy using immune checkpoint inhibitors or driver-based precision medicine. These developments will provide long-term survival to many refractory cancer patients. Improving tolerability of cancer therapy and maintaining quality of life for cancer patients is thought to prolong the healthy life expectancy in patients undergoing prolonged cancer treatment. Most refractory cancer patients suffer from weight loss, fatigue, anorexia and declining physical function due to inadequate catabolism with systemic inflammation. This multifactorial syndrome is defined as cancer cachexia and is characterized by the progressive loss of body weight and reduction in skeletal muscle mass [1, 2]. The incidence of cancer cachexia was estimated to be 50–80% in patients with advanced cancer [3]. In the Japanese lung cancer population, the incidence of cancer cachexia is approximately 50% in those with advanced lung cancer, and body weight loss was related to deteriorated quality of life (QOL) and shortened survival time, regardless of the type of chemotherapy [4, 5]. However, treatment for cancer cachexia has not been well established. A prospective trial to investigate adequate interventions for cancer cachexia patients is urgently needed.

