### Cancer cachexia in elderly cancer patients

The population of elderly cancer patients has been increasing due to a general increase in life expectancy. According to the Surveillance, Epidemiology, and End Results database, more than half of those diagnosed with lung cancer were people older than 70 years [13]. Elderly patients already have reduced physiological skeletal muscle and nutritional status due to aging, resulting in many elderly patients being diagnosed with cancer cachexia. We previously reported that cancer cachexia in elderly patients is strongly associated with decreased activity of daily living (ADL) scores and longer hospitalizations [14]. Furthermore, skeletal muscle depletion during chemotherapy has a negative impact on physical function in elderly non-small cell lung cancer (NSCLC) patients [15]. Because elderly patients independently have a high risk of falls and fractures, careful intervention is necessary for elderly patients with body weight loss and weak skeletal muscle. It is well known that elderly cancer patients are at risk for malnutrition, including cachexia, and they are very fragile when performing daily activities. Therefore, we selected elderly patients with refractory cancer as the participants in this study to investigate multimodal interventions for cachexia, including exercise and nutritional intervention.

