### Aim of the NEXTAC-TWO study

Based on the results of the NEXTAC-ONE study, we hypothesize that early nutritional and exercise interventions with lifestyle consultations will be feasible and will help maintain physical activity levels in elderly patients with advanced cancer who are at high risk of cachexia. We are conducting a randomized trial to elucidate whether the nonpharmacological, multimodal intervention (NEXTAC program) prolongs survival without disability in elderly patients with advanced NSCLC or pancreatic cancer.

The target population of this study is elderly cancer patients. We previously reported that compared with patients without cachexia, cachexic patients have an increased risk of prolonged hospital stays and higher medical costs [14]. It is well known that elderly patients are at high risk for cachexia. The prevention of the progression of cachexia in elderly patients has the potential to not only improve the QOL but also to reduce their medical expenses. There are several established nonpharmacological interventions for community-dwelling elderly populations that are designed to prevent sarcopenia, disability, or falls [18, 19]. This study will be helpful in designing new strategies to prevent cachexia in elderly cancer patients.

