## Methods

### Study design and participants

The NEXTAC-TWO study is a multicenter, randomized phase II study with 130 participants allocated 1:1 to an intervention group or a control group. One hundred thirty patients will be recruited from 15 Japanese institutions according to the inclusion criteria and exclusion criteria listed in Table 1. Participating institutions include public hospitals, university hospitals, and cancer centers in Japan. The list of study institutions is available in Additional file 2. Recruitment began in August 2017 and is expected to be completed in July 2020.

**Table 1 Tab1:** Inclusion and exclusion criteria

Inclusion Criteria	
1) Diagnosis of advanced non-small cell lung cancer or inoperable pancreatic cancer	
2) Scheduled for systemic cancer therapy (i.e. chemotherapy, and/or targeted therapy and/or immunotherapy)	
i. In pancreatic cancer patients, planned systemic chemotherapy only allows of the combination of gemcitabine with nanoparticle paclitaxel.	
3) Eastern Cooperative Oncology Group (ECOG) performance status 0 to 2	
4) Age ≥ 70 years	
5) Body weight of 6 month ago can be confirmed	
6) An expected survival of ≥3 months as judged by investigators	
7) Written informed consent	
8) Adequate organ function	
i. Hemoglobin ≥8.0 g/dl	
ii. Total bilirubin ≤2.0 mg/dl	
iii. Aspartate aminotransferase ≤150 IU/L	
iv. Alanine aminotransferase ≤150 IU/L	
v. Serum creatinine ≤2.0 mg/dl	
vi. Arterial oxygen saturation (SpO_2_) ≥ 90% or partial pressure of oxygen in arterial blood (PaO_2_) ≥ 60 Torr in room air	
vii. Resting heart rate < 120 beat per minute	
Exclusion criteria	
1) Patients received prior chemotherapy except adjuvant chemotherapy	
2) Active malignancy requiring cancer treatment including chemotherapy, radiotherapy and surgery within 3 months	
3) Patients who need nursing care at following situation (based on Katz Index)	
i. Bathing	
ii. Dressing	
iii. Transferring	
iv. Feeding	
4) Symptomatic brain metastasis or leptomeningeal carcinoma	
5) Bone metastasis with high risk of fracture	
6) Patients who are difficult to evaluate or intervene with cardiovascular disease, bone and joint disease, neuromuscular disease etc.	
7) Patients who are difficult to participant due to psychiatric disorder	
8) Patients who are difficult to oral intake	

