#### Nutritional assessment

At every assessment point, body weight (kg) is measured to the nearest 0.1 kg. The registered nutritionist assesses the nutritional status using the full version of the Mini Nutritional Assessment (full MNA®) and estimated ingested nutritional quantity using a 24-h recall method.

Lumbar skeletal muscle mass is measured at T1 and T4 by analyzing electronically stored CT images using the Slice-O-matic software (version 5.0, Tomovision, Montreal, Quebec, Canada) as previously reported [23].

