### Statistical considerations

We set the recruitment period to 3 years, starting in August 2017. All participants who pass the screening are randomly assigned to the intervention group or the control group at a ratio of 1:1 in every stratified group, and they are followed for 2 years after randomization. The levels of stratification factors are as follows: (1) NSCLC or pancreatic cancer, (2) PS = 0/1 or PS = 2, and (3) cytotoxic chemotherapy or not.

With 64 patients per group, the trial achieves 80% power to detect an improvement in median disability-free survival from 8 months in the control group to 12 months in the intervention group using a two-sided log-rank test with a significance level of 0.20. Because we observed only a few dropouts from the NEXTAC program in the phase I study, we estimated the needed sample size with a small number of additional patients included. In total, 130 patients will eventually be included in the study. The disability-free survival and overall survival are estimated using the Kaplan-Meier method. To compare categorical variables, chi-square or Fisher’s exact tests are used. Continuous measures are compared using the Wilcoxon rank-sum test. For the primary endpoint analyses, *p*-values < 0.05 are considered significant.

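### The abstract extends the result to patients with cancer cachexia although an at-risk population is enrolled, and the stated primary comparison makes no use of baseline weight loss, which can be computed for essentially every patient

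*Protocol article*

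**What the plan says.** **The claim.** The abstract's Methods paragraph says the results will demonstrate the efficacy of multimodal interventions in elderly cancer patients and "their application for the maintenance of physical and nutritional conditions in patients with cancer cachexia". The section on cachexia in elderly patients gives the reason for the choice of participants as "to investigate multimodal interventions for cachexia, including exercise and nutritional intervention".

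**The population.** The Aim section describes "elderly patients with advanced cancer who are at high risk of cachexia". Table 1 has no weight-loss threshold and no cachexia criterion. Its one weight item is inclusion criterion 5: "Body weight of 6 month ago can be confirmed".

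**Prognosis.** The Background reports that "the incidence of cancer cachexia is approximately 50% in those with advanced lung cancer" and gives 50–80% for advanced cancer generally. It also says that weight loss was related to poorer quality of life and shorter survival whatever the type of chemotherapy. The section on elderly patients links cachexia to lower activity-of-daily-living scores.

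**Baseline data.** Under Nutritional assessment: "At every assessment point, body weight (kg) is measured to the nearest 0.1 kg". T1 falls before the first systemic treatment.

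**The comparison.** Statistical considerations names a two-sided log-rank test for the sample size and Kaplan-Meier estimation for disability-free survival. Its stratification factors are primary site, performance status and "cytotoxic chemotherapy or not"; the abstract adds stage. Neither list contains weight loss.

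**The concern.** Two things do not fit together.

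First, the abstract extends the result to patients who have cachexia, while the trial enrols patients at risk of it, some with cachexia and some without. The primary comparison gives one effect averaged over both. A positive result would leave open whether cachectic patients benefit, and a null result would not rule it out.

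Second, the article itself names weight loss as related to survival and cachexia as related to daily functioning. Death and loss of daily functioning are the two components of disability-free survival. A baseline variable with that standing, for which the data are already required, is not used in the stated comparison. Because the reported link with survival holds regardless of chemotherapy type, stratifying by chemotherapy type does not replace it. What is at stake is some power and protection against chance imbalance, not the validity of the randomised test.

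**Working it through.** **1. The plan's own figure.** Inputs from Statistical considerations: medians 8 and 12 months, two-sided 0.20, 64 per group, two years of follow-up after randomisation. With exponential survival, HR = 8/12 = 0.667 and |ln HR| = 0.4055.

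- Event probabilities at 24 months: 1 − 2^(−24/8) = 0.875 and 1 − 2^(−24/12) = 0.750, mean 0.8125.
- Events: 128 × 0.8125 = 104.
- Power (Schoenfeld): Φ(0.4055 × √104 / 2 − 1.2816) = Φ(0.786) = 78.4%.
- If follow-up instead runs for 24 months after a 36-month accrual: 118.8 events, power 82.3%.

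The two readings bracket the stated 80%, so the plan's figure is reproduced.

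**2. How mixed the population would be.** Taking the Background's 50–80% as prevalence at entry (an assumption), 130 × 0.50 = 65 down to 130 × 0.20 = 26 patients would not be cachectic.

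**3. Does an effect of 2/3 within each group agree with the plan's medians?** Let half the control patients have hazard λ and half Hλ, so S0(t) = ½e^(−λt) + ½e^(−Hλt), with λ chosen so that S0(8) = 0.5. Multiplying both hazards by 2/3 gives S1(t) = S0(2t/3), so the intervention median is 8 × 1.5 = 12 months for any H. The scenarios below therefore keep the plan's medians of 8 and 12 months.

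**4. Power with and without cachexia in the analysis.** Simulation with 20,000 trials per row, 64 per arm, 50% cachectic, censoring at 24 months, two-sided 0.20. H is assumed.

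| H for cachexia | Log-rank, unstratified | Log-rank, stratified by cachexia | Gain (points) |
|---|---|---|---|
| 1.5 | 77.0% | 78.0% | 1 |
| 2.0 | 73.3% | 77.3% | 4 |
| 2.5 | 69.9% | 76.7% | 7 |

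Separate runs of the same model put the gains at about 1–2, 3–5 and 6–7 points.

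**5. Chance imbalance.** With 50% prevalence and 65 per arm, the standard error of the difference in prevalence is √(2 × 0.25/65) = 0.0877. Then P(|difference| ≥ 0.10) = 2[1 − Φ(0.10/0.0877)] = 25%. The exact binomial calculation with 64 per arm gives 25% for 10 points or more and 9% for 15 or more.

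**6. What a cachexia-specific result could show.** With N = 130, 24 months of follow-up and HR 0.667:

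| Prevalence | Cachectic n | Events | Power at 0.20 | Interaction power at 0.20 (HR 0.667 vs 1) |
|---|---|---|---|---|
| 50% | 65 | 53 | 58% | 41% |
| 80% | 104 | 85 | 72% | 33% |

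At 50% prevalence, an observed HR of 0.667 in the cachectic subgroup would have a 95% interval of about 0.39 to 1.14. Any such result is exploratory.

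**The case against.** **At-risk enrolment is the declared design.** The Aim section says so, and the randomised comparison answers the stated question in that population. A reader might infer that failing to select on cachexia is a design error. The documents do not support that.

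**Randomisation strata.** The abstract's four binary factors already make 16 cells for 130 patients. A fifth would make 32, about four patients each (130/32). Leaving cachexia out of the randomisation is defensible.

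**No prevention result is promised.** The sentence "This study will be helpful in designing new strategies to prevent cachexia in elderly cancer patients" speaks of designing later strategies. A reader might infer that incident cachexia had to be an endpoint; the sentence does not commit the trial to that.

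**Absence of an analysis cannot be shown.** A reader might infer that no analysis by baseline cachexia is planned. This is a condensed article, and covariates and subgroups are often left to the analysis plan. All that can be said is that the article describes none. The translational section implies some classification by cachexia, but for biomarkers only.

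**The premises are soft.** The 50% is called an incidence and is not specific to patients aged 70 or over without disability. The article gives no strength for the prognostic relation. The 25% imbalance probability is ordinary for any unstratified factor of this prevalence and biases nothing.

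All of this stands. It leaves untouched the abstract's extension to cachectic patients and the low cost of using a baseline value that is already obtainable. A further objection, that the loss of power comes only from imposing a conditional hazard ratio, fails: step 3 shows that this assumption keeps the plan's medians.

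**Conclusion.** The point holds in limited form. The abstract's conclusion about patients with cancer cachexia goes beyond the enrolled at-risk population. The stated log-rank comparison forgoes a modest, nearly free gain from baseline weight loss. The size is about 1–2 points of power at a prognostic hazard ratio of 1.5, 3–5 at 2.0 and 6–7 at 2.5, together with protection against an imbalance of 10 points or more that has a probability of about 25%.

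These figures assume 50% prevalence at entry, exponential survival, a common treatment hazard ratio of 2/3, the 0.20 level used for the sample size, and no overlap between cachexia and the existing factors. If performance status and primary site already capture part of the prognosis, the gain is smaller.

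A reader might call weight loss a strong prognostic factor or regard the primary test as invalid. The article gives no strength for the relation, and the unadjusted randomised test remains valid.

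**What to change.** 1. In the disability-free survival analysis, include baseline six-month weight loss as a covariate or analysis stratum alongside the randomisation factors. Use it as a continuous variable or dichotomised at a threshold fixed before the data are examined; the article prints no threshold, so one must be written down. State that the current weight is the T1 value, taken before the first intervention session.
2. Limit the abstract's conclusion to elderly patients with advanced non-small cell lung or pancreatic cancer at risk of cachexia. If an effect by baseline cachexia status is reported, label it exploratory.

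The cost is wording in the analysis plan and one sentence of the abstract. No new measurement or patient is needed, and randomisation is unchanged. Recruitment was still under way in February 2019, so the choice could be fixed before the outcome data are analysed. If the unseen analysis plan already contains item 1, only item 2 remains.

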**Discussion:**

This is the first randomized trial to evaluate the efficacy and safety of a multimodal intervention specific for elderly patients with advanced cancer.

**Trial registration:**

Registered at August 23, 2017. Registry number: UMIN000028801.

**Electronic supplementary material:**

The online version of this article (10.1186/s12885-019-5762-6) contains supplementary material, which is available to authorized users.

## Background

Advances in cancer therapy have been extended not only to combinations of cytotoxic chemotherapy but also to immunotherapy using immune checkpoint inhibitors or driver-based precision medicine. These developments will provide long-term survival to many refractory cancer patients. Improving tolerability of cancer therapy and maintaining quality of life for cancer patients is thought to prolong the healthy life expectancy in patients undergoing prolonged cancer treatment. Most refractory cancer patients suffer from weight loss, fatigue, anorexia and declining physical function due to inadequate catabolism with systemic inflammation. This multifactorial syndrome is defined as cancer cachexia and is characterized by the progressive loss of body weight and reduction in skeletal muscle mass [1, 2]. The incidence of cancer cachexia was estimated to be 50–80% in patients with advanced cancer [3]. In the Japanese lung cancer population, the incidence of cancer cachexia is approximately 50% in those with advanced lung cancer, and body weight loss was related to deteriorated quality of life (QOL) and shortened survival time, regardless of the type of chemotherapy [4, 5]. However, treatment for cancer cachexia has not been well established. A prospective trial to investigate adequate interventions for cancer cachexia patients is urgently needed.

### Standard of care for cancer cachexia

Weight loss is frequently observed in advanced-stage cancer patients not only in the terminal phase but also in the early phase after diagnosis. In the terminal phase, most cachexia patients enter a stage of refractory cachexia, and they are resistant to any type of intervention. Although it is recommended that therapeutic interventions be initiated as soon as possible, there is little evidence concerning the efficacy and safety of early supportive interventions for cachexia in cancer patients.

There are no approved pharmacological interventions for cancer cachexia. On the other hand, some evidence has been reported regarding nonpharmacological interventions for cancer cachexia [6]. A meta-analysis suggested that oral nutritional interventions might be effective for increasing nutritional intake and improving QOL in cachexia patients [7, 8]. A prospective randomized phase II study was conducted to evaluate the efficacy of dietary advice in patients with cachexia [9]. This trial suggested that early dietary advice might be effective at increasing food intake. On the other hand, physical exercise has the potential to improve physical function in cancer patients undergoing chemotherapy [10]. However, these types of unimodal interventions do not improve mortality. Multimodal interventions might be required to improve the mortality rate of elderly patients with cachexia because it is a multifactorial syndrome. Notably, the current consensus report recommends nutritional support with physical exercise interventions as the standard of care for weight loss in cancer patients. Several studies have reported the effectiveness of the combination of nutritional interventions and exercise to maintain physical function and nutrition in patients with cachexia [11, 12]. However, prospective studies on appropriate nutritional support and exercise intensity and content are still inadequate to act on this evidence in clinical practice.

